#### Exclusion criteria

Participants who disagree with the guidelines of the studyDecreased liver function (Child Pugh class B or C)Bad general condition (Eastern cooperative oncology group (ECOG) > 2)Excessive drinkers (more than 20 g of alcohol intake per day)History of decompensated cirrhosisInability to exercise due to severe heart and lung diseases (heart failure, ischemic heart disease, 3rd degree atrioventricular block, chronic obstructive pulmonary disease, severe high blood pressure (> 200/100 mmHg))Inability to exercise due to serious mental illnessUse of insulin sensitizers (sulfonylurea, biguanide, thiazolidinediones, glucagon-like peptide-1 agonist, dipeptidyl peptidase-4 inhibitor) or those who take insulinUncontrolled diabetes (hemoglobin A1c > 10%)

#### Criteria for discontinuing interventions

If participants meet the exclusion criteriaTumor recurrenceParticipants request

### Intervention

A wearable IoT device and a mobile application-equipped exercise program specialized for HCC will be provided. The intervention group will use mISH for 6 months, whereas the control group will receive usual follow-up care for the first 3 months and mISH for the next 3 months. Personal exercise will be permitted during the trial.

### Intervention group

The mobile application, exercise program, and wearable IoT device comprise one intervention. The application uses data input from a wearable IoT device, Dofit (NF-B20, Medi Plus Solution, Seoul, South Korea). Dofit measures heart rate and physical activity (step counts and calories burned) when worn on the wrist. The application provides information on exercise management (aerobic and resistance exercises), activity tracking, diet management, medication management, and health consultation. Screenshots for each domain of the application are shown in Fig. 2. Each domain consists of the following: main page, menu tab, exercise management, activity tracking, diet management, medication management, and health consultation. Researchers will monitor and feedback on exercise performance.

**Fig. 2 Fig2:**
[figure not shown]
Application screenshots. Screenshots of the main page (**a**), menu tab (**b**), exercise management [aerobic exercise (**c**) and resistance exercise (**d**)], diet management (**e**), and medication management (**f**)

#### Exercise management

The application offers aerobic and resistance exercises. For aerobic exercise, when the start button is pressed, the exercise time is recorded and the heart rate during exercise is measured and displayed in real-time. The intensity of aerobic exercises is prescribed at the target heart rate (THR) according to American College of Sports Medicine (ACSM) guidelines [20].

If a participant is enrolled less than 16 weeks after surgery or radiofrequency ablation (RFA), the intensity of aerobic exercise and resistance exercise is designed to increase step by step from week 1 to week 15. From week 1 to week 15, the intensity of aerobic exercise is set to increase from 58 to 68% of maximum heart rate and the intensity of resistance exercise is also set to increase (see Additional file 1). From the week 16 after surgery or RFA, general exercise management begins, and exercise intensity is adjusted according to the RPE.

If a participant is enrolled 16 weeks after surgery or RFA, baseline 6-min walk test (6 MWT) is used to control the initial intensity of exercise. If the baseline 6 MWT result is better than the average level for the same age and sex, the THR for initial aerobic exercise is 72% of the maximum heart rate, and general exercise management begins immediately. If the baseline 6 MWT result is less than the average level for the same age and sex, after maintaining the THR at 68% of maximum heart rate for 1 month, general exercise management begins. The average value of 6 MWT according to age and sex will be calculated using the following formula [21].$$\mathrm{Men }\left(m\right) = \left(7.57 \times \mathrm{ height cm}\right)- \left(5.02 \times \mathrm{ age}\right)- \left(1.76 \times \mathrm{ weight kg}\right)- 309$$$$\mathrm{Women }\left(m\right)= \left(2.11 \times \mathrm{ height cm}\right)- \left(2.29 \times \mathrm{ weight kg}\right)- \left(5.78 \times \mathrm{ age}\right)+ 667$$

In general exercise management, the THR of the next exercise is determined based on the RPE after the end of the previous exercise. If the participant records “very hard” even once, the exercise intensity is decreased, and if the participant records “very light” or “moderate” twice or more, the exercise intensity is increased. Exercise intensity is estimated by a RPE of 13 (a bit hard) to 15 (hard). In patients with hypertension, the THR is set lower. Participants can check their smart band to monitor their heart rate during aerobic exercise. Notifications are sent to them to inform them if the THR is achieved. This is useful to evaluate the participants’ compliance and to monitor if the participants exercise properly by looking for an increase in heart rate.

When general exercise management is started, the intensity of resistance exercise is also adjusted based on RPE and participants need to follow the video clips of exercises. Video exercise starts with a warm-up, resistance exercises using an elastic band, and finishes with stretching (cool-down).

Healthcare professionals and researchers will access exercise logs through a monitoring platform and will provide weekly guidance and positive reinforcement.

#### Activity tracking

Participants can review daily step counts using Dofit. The application displays daily step counts of general walking, fast walking, and running. It calculates and displays the calories burned from physical activity during the day.

#### Diet management

Based on the user’s body mass index, the necessary calories and customized daily diet guides specialized for HCC are provided. When participants enter the type and amount of food they eat, the application displays if the amount of carbohydrates and protein consumed is over or under the expert’s recommendation. Participants can also check if the balance of the food groups they eat is adequate.

#### Medication management

When medications are registered on the application, an alarm for timely medication is provided on the main screen.

#### Health consultation

The participants are informed of precautions necessary and complications that may occur depending on their cancer treatment process, and the app warns of symptoms that require a hospital visit. When participants have questions about their health or exercise, they can consult with physical therapists and physicians.

### Control group

All participants will receive the same brochure previously provided to HCC patients after anticancer therapy (radiofrequency ablation, hepatectomy, transarterial chemoembolization or radiotherapy). It lists guidelines for healthy living post anticancer therapy and diet specifications such as eating a high-protein diet, eating snacks in the late evening, and avoiding very spicy or salty foods and herbal medicines. An acceptable level of exercise intensity is also recommended in the brochure.

### Measurements

Data from electronic medical record will be used. All participants need to answer a self-administered questionnaire that includes a history of hypertension, diabetes, stroke, use of medications, alcohol, and smoking. Height and waist will be measured to the nearest half centimeter. Weight will be measured to the nearest half kilogram. Blood pressure will be measured after at least 10-min resting. The weight and waist will be measured at each assessment point.

Serum blood tests at baseline include the following: platelet count, hemoglobin A1c, fasting blood glucose, insulin, aspartate aminotransferase (AST), alanine aminotransferase (ALT), prothrombin time-international normalized ratio (PT INR), albumin, total bilirubin, alpha-fetoprotein, proteins induced by vitamin K absence of antagonist-II (PIVKA –II), high density lipoprotein cholesterol (HDL), triglyceride, and low density lipoprotein cholesterol (LDL). Among the above items, fasting glucose, insulin, hemoglobin A1c, and lipid profile will be measured at each assessment point.

### Assessments and data collection methods

Assessments, such as blood test (fasting glucose, insulin, hemoglobin A1c and lipid profile), physical activity, and QoL questionnaires, and physical fitness assessments will be carried out at baseline and 3 and 6 months after baseline. A nutritional assessment will be done to determine if there are any nutritional differences between the two groups. Table 1 describes the assessments for each time point.

#### Primary outcome

The primary outcome is the normalized rate of insulin resistance in each group at 3 months. Insulin resistance is estimated by calculating HOMA-IR, which uses the computer-based solution of the model provided by the Diabetes Trials Unit, Oxford Center for Diabetes, Endocrinology, and Metabolism (http://www.dtu.ox.ac.uk/homa). When the HOMA-IR falls below 2.2, it is considered that insulin resistance is normalized.

#### Secondary outcome

The secondary outcomes are the normalized blood test profile (fasting glucose, insulin, hemoglobin A1c), body composition, physical fitness, and patient-reported outcome such as physical activity level, QoL, and adverse events. Data for the body composition analyses is collected using a bioelectric impedance device, Inbody 720 (Biospace). Muscle mass and body fat percentage will be recorded, and body mass index (BMI) will be calculated as body weight/height^2^ (kg/m^2^).

Physical fitness is measured by the grip strength test, the 30-s chair stand test, and the 6 MWT. A digital hand-held dynamometer (microFET® HandGRIP; Hoggan Health, Salt Lake City, UT) is used to assess the upper extremity muscle strength. Seated participants hold the dynamometer in their arm with shoulder adducted, elbow flexed to 90°, and forearm and wrists resting in a neutral position. After 3 s, the maximum power is measured. The experiment is performed on the other side in the similar way. We use an average of the 3 grip strength tests. A 30-s chair stand test is performed to evaluate the strength of the lower extremities. Participants are made to sit straight in a chair without the support of the backrest and with both arms folded across the chest. For 30 s, they complete stand-up and sit-down motions as quickly as possible, and the number of motions is counted. To estimate the level of cardiopulmonary endurance, the 6 MWT is conducted. The total distance walked at maximal speed for 6 min is recorded.

Physical activity levels are objectively measured using the International Physical Activity Questionnaire-Short Form (IPAQ-SF) questionnaire. This questionnaire includes 9 questions on time spent on vigorous and moderate activities and time spent walking or sitting for the preceding 7 days. The total number of metabolic equivalents (METs) per week can be calculated using this questionnaire. The calculated physical activity is classified into 3 IPAQ-SF categories: inactive (< 600 METs), minimally active (≥ 600 to < 3000), and highly active (≥ 3000).

General health-related QoL is assessed by the European Organization for Research and Treatment of Cancer Quality of Life Questionnaire C30 (EORTC-QLQ-C30). The questionnaire includes 30 questions regarding global health status, functional scales, and symptom scales. Higher scores on the general health status and functional scales indicate positive outcomes, while high symptom scales are considered negative. Adverse events are also reported using EORTC-QLQ-C30.

General nutritional status is assessed by the mini nutritional assessment (MNA). The MNA consists of 18 questions derived from four parameters of assessment: anthropometric, general, dietary, and subjective. The total score for the full MNA will fall between 0 and 30 points: 24 and higher indicates a well-nourished patient; 17 to 23.5 indicates a risk of malnutrition; lower than 17 indicates malnutrition.

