**Discussion:**

This study is the first RCT to investigate the effect of mHealth-based home exercise with a wrist-wearable device on insulin sensitivity, physical fitness, and quality of life for HCC patients with insulin resistance. The result of this RCT will confirm not only safety and functional improvement but also biological effect when exercising using mHealth in HCC patients.

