### Statistical analysis

The strategy for statistical analysis is developed under the supervision of a biostatistician at the Samsung Medical Center. Analyses will be performed using an intention-to-treat approach. Descriptive statistics will be used to present baseline characteristics of both groups. For the primary outcome, the proportion of participants in each group with normalized HOMA-IR at 3 months after baseline will be compared using the chi-square test. For the secondary outcomes, changes in blood test (fasting glucose, insulin, hemoglobin A1c and lipid profile), body composition (muscle mass, body fat), physical fitness level (grip strength test, 30 s chair stand test, 6 MWT), physical activity (IPAQ-SF), general health-related quality of life (EORTC-QLQ-C30), and adverse events at 3 months after baseline will be compared by an unpaired *t*-test. In the control group, according to the self-controlled study design, all outcomes after 3 months of usual care and after using mISH for 3 months will be compared by paired *t*-test. In the intervention group, the primary and secondary outcomes of baseline, 3 months, and 6 months of intervention will be analyzed with repeated measured ANOVA to check whether there are significant changes over time. All tests will use a 5% level of significance (*p* < 0.05). Relative risks and 95% confidence intervals are reported for primary outcome.

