This study has several strengths: to the best of our knowledge, this is the first RCT to demonstrate the beneficial effect of mHealth-based exercise with wearable IoT device in HCC patients with insulin resistance. Second, this RCT investigates if there is a biological effect on insulin sensitivity, physical fitness, and QoL. Third, as participants are prescribed longer-term exercise interventions when compared to previous studies, this study can ensure adherence to long-term mHealth-based exercises.

One limitation of this study is that it is difficult to determine the generalizability to other HCC patients because only subjects with complete remission and preserved liver function participate in this study.

In conclusion, the results of this RCT can provide evidence for mHealth to be a safe way to enable exercising by patients with HCC.

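### Adverse events are assigned to a quality-of-life questionnaire and an unpaired t-test, so the stated between-arm comparison counts no events and does not support the announced safety conclusion

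*Protocol article*

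**What the plan says.** **Outcome and instrument.** The Secondary outcome section of the protocol article places adverse events under "patient-reported outcome such as physical activity level, QoL, and adverse events". It then states: "Adverse events are also reported using EORTC-QLQ-C30". Of that instrument it says: "The questionnaire includes 30 questions regarding global health status, functional scales, and symptom scales". Under Assessments and data collection methods, the questionnaires "will be carried out at baseline and 3 and 6 months after baseline".

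**Analysis.** The Statistical analysis section opens its list of secondary outcomes with the word changes and ends it with "and adverse events at 3 months after baseline will be compared by an unpaired" t-test. The same section sends all control-group outcomes to a paired t-test (usual-care period against intervention period). It sends the intervention group's primary and secondary outcomes to a repeated-measures ANOVA over baseline, 3 and 6 months.

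**Conclusion announced.** The abstract's Discussion says: "The result of this RCT will confirm not only safety and functional improvement but also biological effect". The closing paragraph of the main Discussion is milder: "the results of this RCT can provide evidence for mHealth to be a safe way to enable exercising by patients with HCC".

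**The concern.** The instrument and the test are both stated outright, so this is not detail that an article leaves to its full protocol. Together they send adverse events down a route made for continuous scores. Followed as written, the plan produces a difference in mean symptom score and calls it an adverse-event result.

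The Introduction names hepatic decompensation as the risk that patients and doctors associate with exercise in this disease. It also says that the group's previous study reported no complications but had no control group. What this trial can add on safety is therefore the comparison between randomised arms, and that comparison is the one specified wrongly. A reader of the final report could take a null t-test on symptom scores as evidence that events did not differ.

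**Working it through.** **1. Is there a figure in the plan to reproduce?** None for adverse events. The only planning figure concerns HOMA-IR normalisation (Sample size calculation: 30% against 5%, 80% power, 5% level). With the two-sided pooled formula and mean proportion (0.30 + 0.05)/2 = 0.175:

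n = [1.96 × √(2 × 0.175 × 0.825) + 0.842 × √(0.30 × 0.70 + 0.05 × 0.95)]² / 0.25² = (1.053 + 0.427)² / 0.0625 ≈ 35.1, rounded up to 36.

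Then 36/0.9 = 40. The stated 36 and 40 per group reproduce, but they say nothing about safety.

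**2. The two readings of adverse events, set against the stated tests**

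| | Reading A: questionnaire symptom scores | Reading B: discrete events |
|---|---|---|
| Baseline value | Yes, the questionnaire is given at baseline | None; nothing to change from |
| Unpaired t-test of change at 3 months | Coherent, but it is a quality-of-life analysis | Wrong for counts or yes/no data |
| Paired t-test in control group | Coherent for scores | Unsuited to counts or yes/no per period |
| Repeated-measures ANOVA from baseline | Coherent for scores | Needs a baseline value that events lack |
| Counts injury, decompensation or admission | No | Only if recorded elsewhere, and no comparison of such records is stated |

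The word changes might be read as not reaching the last item in its list. That does not help, because the t-test still applies to adverse events.

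Under reading A, suppose a participant is injured in month 2 and has recovered by the 3-month visit. That participant may score the same at both visits and add nothing to the difference. Under reading B, the test does not match the data. Neither reading yields the number of participants with an event in each arm.

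**3. Other places where events might be recorded**
- The retention section offers a 24-hour telephone number.
- Participant safety and withdrawal lets participants call at any time and has them examined for intolerable muscle pain or injury.
- Measurements names the electronic medical record as a data source, but repeats only glucose, insulin, HbA1c and lipids at every assessment. The liver tests are listed at baseline.

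These routes can bring events to light. None comes with a stated between-arm analysis.

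**4. How far any safety statement could go, given perfect capture.** With zero events in n participants, the exact two-sided 95% upper limit is 1 − 0.025^(1/n):
- n = 40: 1 − 0.025^(1/40) = 8.8%
- n = 36: 1 − 0.025^(1/36) = 9.7%

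The documents give no event rates, so power needs assumed ones. With 40 per arm, Fisher's exact test has power of 11% for 2% against 10%, 18% for 5% against 15%, and 41% for 5% against 20%. These figures describe the sample size, not the defect. They bear only on how the conclusion is worded and on keeping the comparison descriptive.

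**The case against.** The strongest reply is that the questionnaire is not shown to be the only source. The word also in the Secondary outcome section, the telephone and visit routes and the medical record leave room for other capture. The full protocol, cited as version 2.3 and available on request, may contain an event form. This stands. A reader might infer that the trial will hold no safety data at all, and the article does not support that. But a form elsewhere would not repair the instrument and the test that the article does state.

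A reader might also infer unequal detection, because researchers "will provide weekly guidance and positive reinforcement" to those using the application, which in months 0-3 means the intervention arm. The article does not say that events are collected at those contacts, and it offers the telephone line to participants without limiting it to one arm. If capture is by the same questionnaire at the same visits, it is symmetric. The unequal-detection reading should not be pressed.

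Third, the 8.8% limit would hold for any arm of 40 and is unchanged by the fix. That is correct, and it is not evidence of the defect.

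Finally, safety is neither the primary outcome nor part of the stated hypothesis, and the abstract's secondary outcomes omit adverse events. That also stands, and the closing paragraph's wording is modest. The abstract's promise to confirm safety is not.

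**Conclusion.** The point holds as a wrongly stated instrument and analysis. Whether adverse events are symptom scores under the wrong name or events sent to an unsuitable test, the stated between-arm comparison does not count events and does not support the abstract's claim that safety will be confirmed.

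Its size cannot be put as a number, because the documents give no event rates. The HOMA-IR comparison and its sample size are untouched. The conclusion rests on taking the Secondary outcome and Statistical analysis sections at their word. It does not assume that the questionnaire is the sole source of events, nor that the arms are observed differently. Even with complete recording, 40 per arm could support only a modest statement on safety.

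**What to change.** 1. Keep the QLQ-C30 symptom scales as quality-of-life outcomes only, and delete the sentence that makes the questionnaire a vehicle for adverse events.
2. In Statistical analysis, remove adverse events from the unpaired t-test list, and exclude them expressly from the paired t-test and the repeated-measures ANOVA.
3. Record events on the existing case report form, with type, onset, severity and relatedness. Ask the same question in both arms at the existing 3- and 6-month visits, and add a review of the medical record.
4. Report the number of participants with at least one event in months 0-3 by arm, with a risk difference and an exact or score 95% interval, as a descriptive comparison.
5. Reword the abstract's Discussion and the closing paragraph of the Discussion so that the safety statement goes no further than the observed confidence limits.

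**Cost.** The analysis and wording changes are a few sentences. The form change needs ethics board approval under the article's own rule for important modifications. The trial started on 16 March 2021, so events before the change could be recovered only from the medical record, and that difference in source should be reported. Power for any between-arm test stays low, which is why the comparison should be descriptive.

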#### Plans to promote participant retention and complete follow-up

In this study, the control group will be given mHealth after 3 months of usual care, a benefit that may reduce the dropout of the control group. In addition, wearable devices will be provided free of charge so that they could be used even after the end of the study. To assist the participants, we will provide 24-h telephone number in the event of a problem and the participants who discontinue or deviate from the protocol will be encouraged to undergo assessments to implement the intention-to-treat data analysis at the end of the study.

